### Setting

The study is performed in the Zwolle region in the Netherlands. This region includes 56 general practices (solo, duo and group practices) with in total 157 general practitioners (GPs), which are all affiliated to a care group 'Medrie’. Integrated care for CVRM is implemented in this region and coordinated by this care group by providing a practical guideline for the implementation of integrated care for CVRM, offering training to the PNs and organizing yearly benchmark meetings. Furthermore, all general practices collaborate with the same regional hospital (Isala Hospital) with dedicated medical specialists involved in organizing integrated care for CVRM. The care group reached an agreement on integrated care for CVRM with the regionally largest health care insurance company for 3 yrs. Implementation of other disease management programmes e.g. for diabetes mellitus and COPD is also organized by the same care group.

From January 2016, all practices were given the opportunity to participate in the integrated care for CVRM. Every 3 months there was a possibility to start with the programme. Participation was not mandatory. Consequently, the intervention was not randomly allocated to the practices. Prior to our study, approximately two third of the general practices (*n* = 37) chose to implement integrated care for CVRM, while the remaining general practices (*n* = 19) will continue usual care due to a variety of reasons. The practices in the usual care group will not have the opportunity to start with the integrated care for CVRM during the study.

This allowed the opportunity to compare integrated care for CVRM (intervention group) with usual care.

### The integrated CVRM programme

The intervention under study is the integrated care programme for CVRM (see Table 1), based on the Dutch CVRM guideline and the practical manual for CVRM provided by the Dutch Society of General Practitioners [7, 21]. The intervention includes features of the Chronic Care Model (CCM), such as self-management support (help patients to set limited goals and identify barriers to reach their goals), regular follow-up, registration of patient data in clinical information systems, a structured, nurse-led health care organization and easy accessible consultation of a specialist [22]. The aim of the integrated care programme for CVRM is to decrease the risk of CVD for patients with a high CV risk or history of CVD by lifestyle treatment and medication if needed. Treatment goals are according to the Dutch guideline for CVRM, including systolic blood pressure < 140/90 mmHg, LDL-cholesterol < 2,5 mmol/L, no smoking, BMI ≤ 25 kg/m2 (< 70 years) or ≤ 30 kg/m2 (≥ 70 years), > 5 days a week moderate intense physical activity > 30 min/day, and a healthy diet (daily 150–200 g vegetables and 200 g fruit; daily 30–40 g dietary fibers; twice a week 100–150 g fish, at least once fatty fish; maximum of 6 g salt per day; maximum of 2 (men) or 1 (women) alcohol consumptions per day).

**Table 1 Tab1:** Elements of the integrated care for CVRM

Element	Contents
Systematic selection of target population	Systematic screening of practice population based on ICPC-codes
	Systematic screening of practice population based on ATC-codes
	Check of medical records according to in- and exclusion criteria of the programme
Active invitation of patients for the programme	Active invitation for an intake consultation by letter
	Reminder in case of no response
Collaboration with different disciplines	Well trained practice nurses, supervised by GPs
	Optional involvement of physiotherapist or dietician
	Online consultation of medical specialist
Data registration in multidisciplinary information system for integrated care (KIS, Portavita®)	Including data on laboratory measurement, intake consultation and follow-up controls
Benchmark meetings	Comparison op patient data of general practice with national data
Laboratory measurement (prior to intake consultation)	Lipids (total cholesterol, HDL-cholesterol, TC/HDL-cholesterol ratio, LDL-cholesterol, triglycerides)
	Renal function (creatinine, GFR estimated by MDRD)
	Glucose
Intake consultation	
Interview	Cardiovascular complaints
	Family history of CVD
	Medication adherence
	Lifestyle
	Motivation to change behaviour
Physical examination	Length, weight, BMI and waist circumference
	Blood pressure
	Pulse rate
Estimation of 10-years cardiovascular risk	Based on the risk chart in the Dutch guideline
cIndividual treatment goals	By shared decision making
General lifestyle advice	According to physical activity and diet
Medication (initiated or adapted if necessary)	Blood pressure lowering drugs
	Lipid lowering drugs
	Anticoagulants
Referral (if necessary)	Smoking cessation programmes
	Dietician
	Exercise programmes
	Physiotherapist
	Medical specialist
Regular follow-up	Evaluation of personal goals
	Adjustment of treatment

#### Organisation strategies of the integrated CVRM programme

The organisation strategies of integrated CVRM programme include:
Systematic identification of patients eligible for CVRMActive invitation of patients for the programmeRegular follow-up of patientsCollaboration with different disciplines in the health care chainRegistration of data in an information system for integrated care

General practices need to systematically organize their practice and identify the eligible population prior to implementation of integrated care for CVRM, based on a regional protocol (‘Organized Practice’) provided by the care group. According to this protocol patients with a history of CVD, at high CV risk (> 10%) or prescribed blood pressure or lipid lowering drugs are included in the programme. To identify the patients, the practice population is systematically screened based on International Classification of Primary Care (ICPC)-coded diagnoses and on Anatomical Therapeutic Chemical-codes (ATC-codes), a classification system for drugs (Tables 2, 3 and 4). Since they already are included in a separate disease management programme, patients with diabetes mellitus (DM) with ICPC-codes T90.01 (DM type I) and T90.02 (DM type II) are not included in the CVRM care programme. Subsequently, medical records of identified patients are manually checked to define whether they meet the in- and exclusion criteria.

**Table 2 Tab2:** ICPC-coded diagnoses for patients with cardiovascular disease

Diagnosis	ICPC-code
Angina pectoris	K74/ K74.01/ K74.02
Acute myocardial infarction	K75
Other/chronical ischemic heart disease	K76
Coronary sclerosis	K76.01
Previous myocardial infarction (> 4 weeks ago)	K76.02
Transient ischaemic attack (TIA)	K89.01
Cerebral infarction	K90.3
Intermittent claudication	K92.01
Aneurysm aortae	K99.01

**Table 3 Tab3:** ICPC-coded diagnoses for patients with high (> 10%) cardiovascular risk

Diagnosis	ICPC-code
Hypertension without organ damage	K86.00
Hypertension with organ damage	K87.00
Disorder of lipid metabolism	T93.00
Hypercholesterolemia	T93.01
Mixed hyperlipidaemia	T93.03
Familial hypercholesterolemia/−lipidaemia	T93.04
Rheumatoid arthritis	L88.01
M. Bechterew	L88.02
Psoriatic arthritis	S91.00

**Table 4 Tab4:** ATC-codes

Medicine	ATC-code
Antithrombotic agents	B01
Cardiac therapy	C01
Blood pressure lowering drugs	C02
Diuretics	C03
Beta blocking agents	C07
Calcium channel blockers	C08
Agents acting on the renin-angiotensin system	C09
Lipid modifying agents	C10A

Once the eligible patients are identified, patients are actively invited by mail for an intake consultation. In this letter, patients are informed about the CVRM programme and invited to make an appointment for an intake consultation. If a patient does not respond to the invitation letter, a reminder is sent.

After the intake consultation, patients are monitored on a regular base in general practice. The frequency of follow-up visits depends on cardiovascular risk and treatment goals of individual patients, but a follow-up visit should be performed at least once a year.

Collaboration with several disciplines in the health care chain, such as GPs, medical specialists, practice nurses and -assistants, dieticians and physiotherapists, is an important focus of the CVRM programme. General practices implementing the integrated care intervention have well trained PNs, who identify the patients, review medical records and interview and examine the patients. All the PNs followed basic training including basic education in CVRM. In addition, some of the PNs followed a specialization course in CVRM, but this is not obligatory. The GP supervises the PNs. A dietician or physiotherapist may be involved if necessary. Also, a hospital specialist can be consulted easily online if necessary. If other disciplines are involved, they are given access to the patient data collected in a multidisciplinary information system for integrated care (KIS, Portavita®). This KIS is also used as a communication platform between the disciplines.

All patient data collected during the intake visit and follow-up visits will be registered in the KIS. These data will be used for benchmark purposes, including comparison of mean systolic blood pressure and LDL-cholesterol levels and smoking rates per practice with national data. Practices receive a benchmark report once a year and benchmark meetings will be organized by the care group.

#### Integrated CVRM programme for individual patients

For individual patients, the integrated CVRM programme includes:
An intake consultationRegular follow-up visitsOptions for referral to get support in changing lifestyle

All eligible patients are invited for an individual face-to-face intake consultation at the general practice. Prior to the consultation, lipids (total cholesterol, HDL-cholesterol, TC/HDL-cholesterol ratio, LDL-cholesterol, triglycerides), renal function (creatinine, glomular filtration rate (GFR) estimated by the formula based on the Modification of Diet in Renal Disease study (MDRD)) and glucose are measured. The consultation consists of several components, including an interview to assess cardiovascular complaints, family history of CVD and difficulties with taking medication. Further, smoking habits, diet, alcohol, physical activity and psychological stress are assessed, as well as the patient’s motivation to change any factor if needed (Table 5).

**Table 5 Tab5:** Assessment of lifestyle during intake consultation

Assessment of lifestyle	
Smoking	• Units per day
	• Smoking history
	• Attempts to quit
	• Motivation to quit
Dietary habits	• Knowledge of healthy dietary habits
	• Insight into own dietary habits
	• Necessity to change dietary habits
	• Motivation to change dietary habits
Alcohol use	• Units per week
	• Knowledge of effects of alcohol use
	• Insight into own alcohol use
	• Necessity to change alcohol use
	• Motivated to change alcohol use
Physical activity	• Days a week
	• Knowledge of importance of physical activity
	• Insight into own physical activity
	• Necessity to change physical activity
	• Motivated to change physical activity
Stress	• Stress symptoms > 3 months
	• Insight into own stress

Physical examination includes measurement of length, weight, (calculation of) BMI, waist circumference, blood pressure (manual or electronic oscillometric measurement, at least 2 measurements with an interval of 1–2 min) and pulse rate.

For patients without CVD an up-to-date 10-years CV morbidity and mortality risk based on the risk chart in the Dutch guideline (based on the SCORE risk function) will be estimated [5].

During the intake visit, individual treatment goals are determined, regarding smoking, physical activity, dietary habits, weight, BMI, blood pressure and LDL-cholesterol. These treatment goals are set by shared decision making between the caregiver and the patient based on the Dutch guideline for CVRM within the context of a patient’s personal preferences. If indicated, treatment with medication, including blood pressure and lipid lowering drugs, and anticoagulants will be initiated. All patients will be given general lifestyle advice by the PN. Patients not achieving a healthy lifestyle according to the Dutch guideline can be referred to smoking cessation programmes, dieticians and exercise programmes or a physiotherapist to get support in changing their lifestyle.

After the intake consultation, patients will be monitored on a regular base in general practice to evaluate and when necessary adjust their personal goals. At least once yearly, all measurements including estimation of the 10-years CV risk will be repeated.

### Usual care

Usual care is based on the Dutch CVRM guideline, describing how to calculate the CV risk and advice to lower this risk by lifestyle intervention and/or medication. However systematic identification of patients eligible for CVRM, actively inviting patients for a visit, regular follow-up and standardized collaboration with other disciplines in the health care chain are not routinely part of usual care. Usual care practices may work with a PN. Most PNs in the Netherlands have had a basic training in CVRM. Furthermore, data are not registered in an information system for integrated care and GPs do not participate in benchmark meetings.

### ZWOT-CASE study population

The ZWOT-CASE study population will consist of a subgroup of 370 patients from the integrated CVRM care group (intervention) and 370 patients in the usual care group. Both groups consist of respectively i) 185 patients with known CVD and ii) 185 patients with a high (> 10%) 10 yr risk of CVD morbidity and mortality based on the Dutch Guideline for CVRM [7, 23, 24].

Inclusion criteria for patients with CVD:
Patients with a history of atherosclerotic CVD defined as documented angina pectoris, myocardial infarction, chronic ischemic heart disease, coronary sclerosis, transient ischaemic attack (TIA), cerebral infarction, intermittent claudication or aneurysm of the abdominal aortaThe CV risk of the patient is managed in primary care, not in the hospital or outpatient clinic by a medical specialistAge between 40 and 80 years

Inclusion criteria for high risk patients:
Use of blood pressure lowering or lipid lowering drugsA 10 -years CV risk > 10%, based on the Dutch guideline for CVRM and i) either 1 strongly cardiovascular risk enhancing factor or 2 mildly cardiovascular risk enhancing factors (see Table 6) or ii) > 1 CV risk factor (current smoking, SBP > 140 mmHg, LDL >  2.5 mmol/L, TC/HDL-ratio > 8, chronic renal impairment (age <  65 years: eGFR < 60 ml/min/1,73 m2; age ≥ 65 years: eGFR < 45 ml/min/1,73 m2, and/or (micro)albuminuria).A 10-year CV risk of > 20% and > 1 CV risk factor (current smoking, SBP > 140 mmHg, LDL >  2.5 mmol/L, TC/HDL-ratio > 8, chronic renal impairment (age <  65 years: eGFR < 60 ml/min/1,73 m2; age ≥ 65 years: eGFR < 45 ml/min/1,73 m2, and/or (micro)albuminuria).The CV risk of the patient is managed in primary care, not in the hospital or outpatient clinic by a medical specialistAge between 40 and 80 years

**Table 6 Tab6:** Risk enhancing factors [7]

	Not risk enhancing	Mildly risk enhancing	Strongly risk enhancing*
First-degree relative with CVD	No	1 family member < 65 years	> 2 family members with CVD < 65 years or 1 < 60 years
Physical activity	≥ 30 min/d, ≥ 5 d/wk	< 30 min/d, ≤ 5 d/wk	Sedentary
Body mass index	BMI < 30 kg/m2	BMI 30–35 kg/m2	BMI > 35 kg/m2
eGFR	< 65 years: > 60 ml/ min/1,73 m2	< 65 years: 30–60 ml/ min/1,73 m2	All ages: < 30 ml/ min/1,73 m2
	≥ 65 years: > 45 ml/ min/1,73 m2	≥ 65 years: 30–45 ml/ min/1,73 m2	

*CVD* = Cardiovascular disease; *eGFR* = estimated glomerular filtration rate; *d* = day or days; *wk*. = week. *In patients with rheumatoid arthritis a high disease activity is a strongly risk enhancing factor

Exclusion criteria for all patients:
Diabetes mellitus, as these patients are already included in a disease management programme for diabetes mellitusLimited life expectancy, as assessed by the GPCognitive impairment, as assessed by the GPNo Dutch language proficiencyStaying abroad for longer than 3 months during the duration of the study.The CV risk of the patient is managed in the hospital or outpatient clinic by a medical specialist

### Recruitment of patients for the ZWOT-CASE study

The source population consists of 56 general practices. All practices were invited to participate in the study. Eventually, 26 general practices agreed to participate (17 in the intervention group and 9 in the usual care group).

#### Intervention group

Between September and December 2016 general practices randomly invited eligible patients for an intake visit for the integrated CVRM programme. After 1 yr of follow-up, these patients are invited for the study until enough patients are included. The invitation for the study will be sent just before the yearly follow-up visit in the CVRM programme. This visit will be used as the endpoint visit for the study. Just before this follow-up visit, the patients receive a letter from their GP to inform them about the study. If the patient agrees to participate, informed consent is obtained during the follow-up visit.

Patients will be selected in such way, that 50% will be below 65 years and 50% over 65 years, to achieve a reasonable distribution across age categories.

#### Usual care group

In order to create the same study population as in the intervention group, we identify patients in the usual care group according to the protocol (‘Organized Practice’) as described before, including systematically screening of the practice population based on ICPC-coded diagnoses and ATC-codes, and manually checking of medical records. As the general practices in the usual care group do not start with the integrated care programme for CVRM, patients in the usual care group will not be invited for an intake consultation at baseline. Subsequently, a risk profile based on complete data on age, sex, smoking status, blood pressure and lipid spectrum may be missing. In that case, patients can be included if the 10-yeas risk is at least 10%, based on the data that are available. For example, a 55-year old male patient with a missing smoking status and missing total cholesterol/ HDL- cholesterol ratio can be classified as having a CV risk > 10% based on a known systolic blood pressure of 160 mmHg.

Patients in the usual care group are matched to patients in the intervention group. Therefore, the patient in the usual care group will only be invited for the study after the patient in the intervention group agreed to participate. Patients in the usual care group will be invited by letter and subsequently by telephone. If this patient does not agree with participation in the study, the second matched patient from the usual care group will receive an invitation. If the second matched patient also does not agree with participation, we will randomly invite one of the remaining patients from the usual care group who were not invited for the study.

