### Study procedures

Patients will be identified at the beginning of the study in order to be able to analyse factors such as mortality and comorbidity during follow-up. The study starts when patients in the intervention group visit the general practice for an intake consultation (t = 0). After the intake visit the 1 yr follow-up period commences. After 1 yr of follow-up, patients are invited for an endpoint visit. A questionnaire will be attached to the invitation letter.

Prior to the endpoint visit, all patients who agree with participation in the study will be asked to fill out the questionnaire at home. The timeline of the study procedures is represented in Fig. 1.

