### Statistical analyses

The aim of the main analysis is to compare the SBP and LDL-cholesterol levels after 1 yr of follow-up between patients in the intervention group receiving integrated care for CVRM and the patients in the usual care group receiving usual CVRM care. For the main analysis we will use linear regression. For secondary outcomes, linear regression will be used for continuous outcomes, logistic regression for dichotomous outcomes and multinomial logistic regression for categorical outcomes. All analyses will be corrected for clustering.

Given that patients of clusters of patients are not randomly allocated to the intervention or usual care group, we anticipate that differences in baseline risk might be present between both groups. Hence, we will adjust the analyses for these confounders, including patient characteristics and practice characteristics. To do such adjusted analysis we a priori define the following baseline covariates which are well-known to be related to the outcomes: i) patient characteristics, including relevant medication use, such as blood pressure lowering drugs [32], anticoagulants [33] and lipid lowering drugs [34], relevant comorbidity, including COPD [35], heart failure [36, 37], atrial fibrillation [38], renal failure [39], ii) practice characteristics, such as involved disciplines in CVRM care (including number of PNs) [31], number of patients, and number of GPs. Results will be reported both without (i.e. crude results) and after correction for confounders. Confounders are defined a priori and not selected based on statistical significance.

Furthermore, we will examine whether the effect of the integrated care for CVRM is modified by differences in the following practice characteristics: practice organization (solo/duo/group), availability of CVRM protocol and existence of other disease management programmes (COPD, DM). This will be done by adding interaction effects.

All analyses are applicable to patient data matched on age and gender.

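### Inviting usual-care patients only after their matched partner has agreed makes their endpoint visits tend to fall later, and neither matching nor the listed covariates allow for season in SBP

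*Protocol article*

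**What the plan says.** All references are to the protocol article.

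- **Intervention group, timing.** "Between September and December 2016 general practices randomly invited eligible patients for an intake visit for the integrated CVRM programme". A year later, "The invitation for the study will be sent just before the yearly follow-up visit in the CVRM programme", and that yearly visit serves as the endpoint visit. "If the patient agrees to participate, informed consent is obtained during the follow-up visit".
- **Usual care group, order.** "the patient in the usual care group will only be invited for the study after the patient in the intervention group agreed to participate". Contact is made first by post and then by phone. After a refusal the second match is approached, and after a second refusal a random remaining patient.
- **Matching.** The factors are five-year age band, gender and risk group. Calendar date is not among them.
- **Study procedures.** t=0 is defined by the intervention patient's intake consultation. For usual care the section gives no t=0 of its own and no visit window, only that "After 1 yr of follow-up, patients are invited for an endpoint visit".
- **Sample size calculation.** The expected response is 70% in the intervention group and 50% in usual care. The target SBP difference is 5 mmHg. Usual-care levels are assumed to remain stable.
- **Statistical analyses.** The main analysis is linear regression on the one-year levels, corrected for clustering. The covariates are baseline medication, comorbidity and practice characteristics. "Confounders are defined a priori and not selected based on statistical significance". Visit date, season and follow-up time are not listed.

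**The concern.** The waiting step applies to one arm only. An intervention patient is seen at a visit that is due anyway. The usual-care slot opens only once that patient has agreed, and it may then need several rounds of letter and telephone. The delay therefore runs in one direction and is tied to arm.

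If SBP varies over the year, a systematic difference in measurement date adds to, or subtracts from, the estimated programme effect on a primary outcome. The study is not randomised and relies on matching and covariate adjustment to make the arms comparable. A date imbalance created by the recruitment rule itself is one that neither tool, as described, would remove.

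**Working it through.** The article gives no lag and no seasonal figure, so there is no stated number to reproduce. The check shows what the rule implies and how far the result depends on assumptions.

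**Step 1: invitations per usual-care slot.** Input: response p = 0.50 (Sample size calculation). If successive invitations are independent:
- filled by the first invitation: p = 0.50
- filled by the second: p(1 − p) = 0.50 × 0.50 = 0.25
- filled later: (1 − p)² = 0.25
- mean number of invitations: 1/p = 1/0.50 = 2

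Half of the slots need at least two consecutive rounds.

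**Step 2: lag.** Assumption: one round takes 1, 2, 4 or 6 weeks. Mean lag behind the partner's agreement = weeks per round × 2 = 2, 4, 8 or 12 weeks. At 4.345 weeks per month this is about 0.5, 0.9, 1.8 or 2.8 months, which is covered by a range of 0.5 to 3 months.

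**Step 3: seasonal shift in SBP.** Assumptions: a cosine season with a mid-January peak, f(x) = (S/2) cos(2π(x − 0.5)/12), with x in months from 1 January and S the peak-to-trough swing; intervention endpoint visits spread evenly over a four-month window; usual-care visits in the same window moved by L months.

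The mean of f over a four-month window centred at c is (S/2) × k × cos(2π(c − 0.5)/12), where k = sin(π/3)/(π/3) = 0.827. Hence

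shift = (S/2) × 0.827 × [cos(2π(c + L − 0.5)/12) − cos(2π(c − 0.5)/12)].

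Example for September to December (c = 10), S = 8, L = 2: 4 × 0.827 × (0.966 − 0.259) = 2.34 mmHg.

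Usual care minus intervention, in mmHg; positive values favour the programme:

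| Intervention visit window | Swing S | L = 0.5 | L = 1 | L = 2 | L = 3 |
|---|---|---|---|---|---|
| September to December | 2 | 0.20 | 0.37 | 0.58 | 0.58 |
| September to December | 8 | 0.80 | 1.48 | 2.34 | 2.34 |
| One month later | 2 | 0.13 | 0.21 | 0.21 | 0.00 |
| One month later | 8 | 0.53 | 0.86 | 0.86 | 0.00 |
| Two months later | 2 | 0.03 | 0.00 | −0.21 | −0.58 |
| Two months later | 8 | 0.11 | 0.00 | −0.86 | −2.34 |

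In the first window the range is 0.2 to 2.3 mmHg, or 0.20/5 = 4% to 2.34/5 = 47% of the target difference. In the last it is between about +0.1 and −2.3 mmHg.

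**Step 4: which window applies.** The September to December 2016 dates belong to the invitations for intake. The patient then makes an appointment, non-responders get a reminder, and laboratory tests precede the intake. Intakes, and the visits a year later, may therefore run later than September to December by an unstated amount. The document does not settle which rows of the table apply.

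**The case against.** Several arguments on the other side are sound and limit the point.

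- **Not every usual-care visit need come later.** The trigger is the partner's agreement, not written consent. The letter goes out before the yearly visit, and patients who agree complete the questionnaire at home beforehand. A usual-care invitation could therefore leave before the partner's visit. The rule creates a tendency, not a certainty.
- **Triggering pair by pair keeps dates loosely aligned.** The imbalance is limited to the recruitment lag. It is limited, not removed, because nothing comparable delays the intervention arm.
- **The extra time in usual care matters little by itself.** The plan assumes stable usual-care levels, and the intervention endpoint is a routine yearly visit with no exact 12-month window. A reader might infer that the one-year comparison is broken; the text does not support that. Season is the route that matters.
- **Timing terms are often left to an analysis plan.** The covariate list is worded openly and concerns baseline confounders, so a missing term alone would be no finding. What stands is that the recruitment rule is fixed in this document, creates the imbalance, and meets no counterpart in the matching or in the a priori list.
- **Obvious remedies have drawbacks.** If arm and follow-up length are linked, time since t=0 in the primary model is close to a proxy for arm and would cost precision. Inviting both partners in parallel would enrol some usual-care patients whose partner declines (30% expected), which works against matched recruitment.

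**Conclusion.** The point holds as a risk of seasonal bias in the SBP comparison, of unstated size and direction. The document establishes the one-sided invitation order, the replacement steps at 50% response, and the absence of measurement date from both the matching factors and the listed covariates. The lag per round, the seasonal swing and the mid-January peak are assumptions.

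A reader might infer that the bias favours the programme. That needs endpoint visits in September to December, whereas the article dates only the intake invitations; visits two months later bring the shift to about zero or reverse it. A reader might also carry the concern over to LDL-cholesterol, but nothing in the document gives a mechanism or a figure for it. Since the sign cannot be settled in advance, adjusting for date is safer than arguing about its direction. This is a change worth making, not a flaw that invalidates the design.

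**What to change.** 1. Record the date of the endpoint measurement in both arms. Endpoint data already go into the electronic medical record.
2. State that usual-care t=0 is the matched partner's intake date, so that follow-up time is defined in both arms.
3. Add calendar month of the endpoint measurement, or a seasonal term, to the prespecified covariates of the primary SBP model, and to the LDL model for consistency.
4. Report the distribution of measurement dates and of follow-up time by arm. Use time since t=0 only in a sensitivity analysis.

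The cost is one extra covariate, with a small loss of precision. Recruitment need not change. Parallel invitation on the partner's intake anniversary would shorten the lag, but it is a trade-off against matched recruitment and is not needed for this fix.
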